#### Recruitment.

**Fracture patients.** We will draw our case sample from patients undergoing surgery at IU Methodist Hospital with fractures of the ankle. We have a HIPAA waiver of consent for screening. IU Methodist Hospital Orthopedic research staff will review daily inpatient and outpatient OR schedules to screen for potentially eligible participants. We will be using the hospitals’ electronic medical records to obtain this information. Potentially eligible patients will be called on the phone by a member of the study team after their surgery but before their first post-operative appointment at the outpatient orthopaedic clinic. For those that express initial interest on the phone, study procedures, purpose, and inclusion/exclusion criteria will be reviewed. For those still interested, the patient will be given the following options:

1) provide verbal consent over the phone and then complete several patient-reported outcomes over the phone or online prior to the first in-person visit. A verbal script will be used when consenting subjects over the phone. Also, subjects who consent verbally will be sent the consent form via email to have during the phone call. Written consent is obtained during the first in-person visit.2) wait to provide any type of consent until the first in-person visit. In this case, all patient-reported outcomes are not completed until the in-person study visit after the written informed consent is obtained.

**Controls.** Our study will recruit control subjects by being listed on the Indiana Clinical and Translational Sciences Institute (CTSI) study listing called the All IN for Health TrialX iConnect. iConnect is a HIPAA-compliant and secure public facing research recruitment platform provided by the Indiana CTSI consisting of a study trial listing and volunteer registry. This system is licensed by Indiana University from TrialX and is monitored by the Indiana University Information Technology Services (UITS) and University Information Security Office (ISO). Study Teams have access to their study listings and participant referrals based on a secure login. This online platform provides researchers with the ability to create a public facing webpage that allows the public to refer themselves to the trial: (https://research.indianactsi.org). The study listings are open to the public and any persons who visit our study page may submit their contact information to the study team through the listing. We will also recruit participants with IRB-approved flyers. Individuals interested in being a control subject will email or call the research staff. For those that express initial interest on the phone/email, study procedures, purpose, and inclusion/exclusion criteria will be reviewed. For those still interested, the individuals will be given the following options:

1) provide verbal consent over the phone and then complete several study related questionnaires over the phone or online prior to their one time in-person visit. A verbal script will be used when consenting subjects over the phone. Also, subjects who consent verbally will be sent the consent form via email to have during the phone call. Written consent is obtained during the in-person visit.2) wait to provide any type of consent until the in-person visit. In this case, all patient-reported outcomes are not completed until the in-person study visit after the written informed consent is obtained.

### Procedures

See Table 3 for a list and timeline of study procedures for fracture patients. Our patient reported outcomes were chosen to align with the NIH HEAL Initiative (The Helping to End Addiction Long-term) common data elements [21].

**Table 3 pone.0327605.t003:** Calendar of study procedures for fracture patients.

	Daily	Standard of Care Follow-up			
		2-4** weeks	5-9** weeks	3-5** months	6-9** months
Screening	X				
Consent		X			
Inclusion/Exclusion criteria review^		X	X	X	X
Patient Characteristics form***		X			
Medical History form		X			
AIS form		X			
Injury Characteristics form****		X			
Clinical Follow-up form (fracture complications and healing) *****			X	X	X
Participant Follow-up form			X	X	X
Thermography		X	X	X	X *
Blood draw		X	X	X	X *
Quantitative sensory testing			X	X	X *
Immune cell analysis		X	X	X	X *
Chronic Pain Grading Scale				X	X
DNF – Interview				X	X
Ankle OA scale				X	X
Pain Map		X	X	X	X
Foot and Ankle Disability Index		X	X	X	X
Pain Catastrophizing Scale		X	X	X	X
PROMIS – Pain intensity		X	X	X	X
PROMIS – Pain Interference		X	X	X	X
PROMIS – Pain Behavior		X	X	X	X
PROMIS – Anxiety		X	X	X	X
PROMIS – Depression		X	X	X	X
PROMIS – Physical Function		X	X	X	X
PROMIS – Neuropathic Pain Quality		X	X	X	X
PROMIS – Sleep Disturbance		X	X	X	X

^Inclusion/Exclusion criteria review will occur prior to patient enrollment via a) medical record review to identify potential fracture participants and b) possibly over the phone. **All patient reported outcomes (PROs) may also be completed over the phone or online at each timepoint, if the patient prefers. *Only performed if session is in person vs. over phone. ***Age, gender, race, education level, socioeconomic status, workman’s compensation status. ****Open/Closed fracture classification, fracture description (both classic and AO/OTA classifications). *****Infection, nonunioun, post-traumatic arthritis, re-operation. At 1 to 1.5 years, we will review the patient’s medical record to assess for complications and we will contact by phone those determined to have BFNP to assess other PROs to see if their clinical pain state has resolved.

#### Screening and enrollment visit for fracture patients (1^st^ visit, 2–3 weeks post-surgery).

The patient will complete the written informed consent document for the study at their 1^st^ post-operative standard of care visit with the first study visit completed in conjunction/right after the 1^st^ post-operative standard of care visit. At the first post-operative visit and over the phone (if applicable), study staff will review the informed consent and provide a clear explanation about what the study involves and its risks and benefits. Participants will be encouraged to take sufficient time to ask questions and to consider whether to volunteer to participate. We will also inform subjects about HIPAA regulations. Subjects will be asked to sign an Informed Consent Form to grant authorization for collection of health data. Those individuals who sign the forms will be enrolled in the study. Participant will be provided a written copy of the consent form. The remaining procedures of this visit are listed in Table 1 and further described below.

#### Follow-up visit(s) – Fracture patients only.

The first three follow-up visits will be in-person visits and will be completed within the time frame of 5−9 weeks, 3−5 months, and 6−9 months post-ankle fracture surgery. Lastly, the fourth follow up will be a phone call follow-up at 1–1.5 years post-ankle fracture surgery. The procedures of each visit are listed in Table 1 and further described below.

#### Control subjects study visit.

At the in-person study session, study staff will first review the informed consent and provide a clear explanation about what the study involves and its risks and benefits. Participants will be encouraged to take sufficient time to ask questions and to consider whether to volunteer to participate. Subjects will be asked to sign an Informed Consent Form. Those individuals who sign the form will be enrolled in the study. Participants will be provided a written copy of the consent form. All control subjects will only participate in one single study visit. During the visit, controls will complete the following procedures: inclusion/exclusion criteria review, Patient Characteristics form, Medical History form, thermography, blood draw, quantitative sensory testing, pain map, Pain Catastrophizing Scale, and all PROMIS questionnaires except for the Neuropathic Pain Quality questionnaire.

### Outcome measurements

#### Measurement of BFNP in fracture patients.

The Chronic Pain Grading Scale (CPGS) will be used to determine whether fracture patients have chronic pain in the chronic phase of injury (3–5 month visit and 6–9 month visit). Fracture patients who report persistent pain (non-zero score on the CPGS) at 3–5 months and 6–9 months will also complete the Douleur Neuropathique 4 (DN4) questionnaire at the 3–5 months and 6–9 month visits.

**Chronic Pain Grading Scale (CPGS).** The CPGS grades chronic pain as a function of pain intensity and pain-related disability reported by the participant for the last three months [22]. The subscale score characteristic pain intensity will be used to categorize participants into those with and without chronic pain [23]. This item is the sum of three questions (current pain, worst pain, average pain over last month), each scored on an 11-point Likert scale with responses ranging from 0–10 for a maximum of 30 points. The participant will be asked to report only on pain related to the site of fracture. Participants scoring 1–30 on the characteristic pain intensity score in the last month at the site of fracture will be classified as having chronic pain. Patients reporting no pain (0) at the site of fracture in the last month will be classified as having no chronic pain. This tool has been used to assess chronic pain following trauma [23–25]. Internal consistency is acceptable with Cronbach’s alpha ranging from 0.67 to 0.74 depending on chronic pain condition and Kappa coefficient from 0.79 to 0.86. The CPGS has also shown good concurrent and prognostic validity [22,26].

**Douleur neuropathique 4 (DN4).** The DN4 is a validated and reliable screening tool for neuropathic pain consisting of 7 items [27,28]. The items relate to pain quality (i.e., sensory and pain descriptors) and are based on interview with the patient. The items of the DN4 are scored based on a yes (1 point)/no (0 points) answer. This leads to a score range of 0–7. The cut-off value for the classification of neuropathic pain is a total score of >3 [28,29]. The DN4 has been used to identify neuropathic pain in ankle and wrist facture patients [7,19].

#### Blood collection for pro-inflammatory mediators.

For visits 1–4, a site research nurse will collect up to 450 mL of blood using standard protocols. Blood specimens are considered routine safety laboratories and will include EDTA anticoagulant tubes for plasma analysis and PAXgene for RNA sequencing. This blood will be assayed for the presence of pro-inflammatory mediators.

#### Thermography assessment.

For visits 1–4, differences between the two ankles will be measured at room temperature (23°C), with subjects kept in an upright position for 15 min to obtain sympathetic equilibrium. A thermographic image of the ankles will be taken using an infrared camera from a distance of 70 cm. Thermography is a noninvasive tool that uses an infrared camera to produce images that show patterns of heat and blood flow on or near the surface of the body.

#### Quantitative Sensory Tests (QST).

Subjects will be made familiar with each sensory test to be performed and will be taught the 0–100 pain rating system. Subjects are not expected to experience severe pain during the QST procedures as the temperatures and pressures to be used are below the pain tolerance levels observed in human studies. The sensory detection and pain threshold test will be performed first followed by the temporal summation test and then the conditioned pain modulation (CPM) test. Sensory and pain detection thresholds will be measured on the skin proximal to the level of ankle injury to assess neuropathy severity, as well as the contralateral uninjured side to serve as a within subject control. A trained research coordinator will perform the testing. Specifically, the following measures will be administered based on the guidelines provided by the German Research Network in Neuropathic Pain [30]: cold and warm detection and pain thresholds and mechanical detection thresholds. These measures are effective in characterizing small (Aδ, C) and large fiber (Aβ) sensory deficits. We will also administer two of the most extensively studied paradigms to measure endogenous pain modulation in humans: temporal summation (TS) and conditioned pain modulation (CPM), which represent ascending facilitatory and descending inhibitory aspects of central pain processing, respectively [31].

**Mechanical detection thresholds.** Mechanical detection thresholds will be examined using von Frey monofilaments, with each filament applied three times in ascending sequence until the threshold is detected in at least two of the three trials. Then, the next lower von Frey filament will be applied, and the lowest filament to be detected at least twice will be determined as the mechanical detection threshold. The subject will close his/her eyes during the test.

**Thermal detection thresholds and pain thresholds.** Warm/Cold detection thresholds and heat/cold pain thresholds will be detected using the Q-Sense/Small Fiber Test (Medoc Advanced Medical Systems, Medoc Ltd, Israel). The thermode temperature will increase (heat) or decrease (cold) from a baseline temperature of 32^o^C with a rise/fall rate of 0.5 °C/s. Participants will be instructed to signal when the stimulus is first perceived as warm/cold. Participants will also be instructed to signal when they first feel the transition from heat to the sensation of heat pain (heat pain threshold) or the transition from cold to the sensation of cold pain (cold pain threshold). Two trials of each will be performed at each ankle.

**Pressure pain thresholds.** A digital, handheld, clinical grade pressure algometer will be used for the mechanical procedures (AlgoMed, Medoc Ltd, Israel). The experimenter will apply a slow constant rate of pressure and record the pressure in kilopascals when the subject responds. Pressure will be applied using a 0.5 cm^2^ probe. Subjects will be instructed to respond when they first feel pain and that pain threshold will be recorded. Two consecutive measurements at each point with intervals of 20 s will be obtained.

**Mechanical temporal summation of pain (TS).** TS will be administered on the skin proximal to the level of injury and the contralateral uninjured side to serve as a within subject control. TS can be assessed by administering short-duration repeated noxious stimuli of a constant intensity and measuring the consequent increase in pain as an indirect method of evaluating hyperexcitability of the central nervous system [32]. First, a single pinprick stimulus using a von Frey filament of 6.65 Mn or 300 g will be applied to the body site. Participants will rate the perceived pain intensity using a numeric rating scale of 0 (no pain at all) to 100 (worst pain imaginable). Then, a series of 10 pinprick stimuli (6.65 Mn) will be administered at a rate of 1 Hz, applied to the body site within an area of 1 cm^2^. The temporal summation value will be calculated as the difference between the first and last stimuli. Two TS trials at each body site will be performed.

**Conditioned pain modulation.** The most frequently used test of endogenous pain inhibition is condition pain modulation (CPM). CPM refers to the reduction of pain produced by a test stimulus by a second noxious conditioning stimulus in a remote body site (i.e., “pain-inhibition-by-pain”) [33]. CPM will be assessed by determining the ability of a cold-water bath (conditioning stimulus) to diminish pressure pain thresholds (test stimulus) applied at a separate body site. After the first trials of pressure pain thresholds on the left forearm, the contralateral hand will be placed into a cold-water bath for 60s. Then, the second trials of pressure pain thresholds will begin on an adjacent site of the left forearm. *Test stimulus*: Two trials of pressure pain thresholds will be administered on the left volar forearm. A digital, handheld, clinical grade pressure algometer with a.5 cm^2^ probe will be used for the mechanical procedures (AlgoMed, Medoc). The experimenter will apply a slow constant rate of pressure and record the pressure in kilopascals when the subject responds. Subjects will be instructed to respond when they first feel pain and pressure at threshold will be recorded. *Conditioning stimulus*: Participants will immerse their right hand up to the wrist in a cold-water bath maintained at 10^o^C for up to 1 minute or until they report intolerable pain (we do not expect this to happen because of the moderately cold water used). Cold pain will also be assessed every 15-sec. The dependent variable for the CPM test will be the change in pressure pain threshold of the test stimulus following the conditioning stimulus.

#### Patient reported outcomes.

The following questionnaires may be administered on paper, over the phone, or by electronic format (REDCap) via email.

**Pain Catastrophizing Scale (PCS) – Adult version.** The PCS assesses negative mental responses to anticipated or actual pain [34]. The PCS has 13 items that are scored on a Likert scale with three subcategories: rumination, magnification, and helplessness. Higher PCS scores are indicative of higher pain catastrophizing. Scores on the PCS have been associated with clinical and experimental pain measures [35].

**Body Pain Map.** Participants will locate the areas of the body that they are experiencing pain on an anatomical map of the body [36]. Females will complete a female body map, while males will complete a male body map. The maps present two side-by-side posterior and anterior pictures of the body with a line separating the left and right sides.

**Ankle Osteoarthritis Scale.** The Ankle Osteoarthritis Scale is a reliable and valid self-assessment instrument that specifically measures patient symptoms and disabilities related to ankle arthritis [37].

**Foot and Ankle Disability Index (FADI).** The FADI is designed to assess functional limitations related to foot and ankle conditions [38]. The FADI contains 26-items, in which each item is scored from 0 (unable to do) to 4 (no difficulty at all). The 4 pain items are scored 0 (unbearable) to 4 (none). This index has excellent reliability and good validity.

**Patient-Reported Outcome Measurement Information System (PROMIS).** PROMIS is a system of item banks developed by NIH to standardize measurement of patient reported outcomes [39–41]. The PROMIS computer adaptive tests (CAT) will be used to measure pain interference, pain behavior, depression, anxiety, and sleep disturbance. The PROMIS CAT system uses Item Response Theory to develop sample-independent scores that are valid across patients with different demographic characteristics. Other PROMIS tools will be used to measure pain intensity and neuropathic pain quality. The following PROMIS tools will be completed at each visit:

a. **Pain intensity** to measure self-reported current, average, and worst pain in the last seven days on a 5-point scale (none, mild, moderate, severe, or very severe) [39–41].b. **Pain interference** to measure self-reported effects of pain on social, cognitive, emotional, physical, and recreational aspects of a person’s life from a bank of 40 items [39–41]. The participant rates interference from pain in the last seven days on a 5-point scale (not at all, a little bit, somewhat, quite a bit, very much).c. **Pain behavior** to measure self-reported external manifestations of pain; behaviors that typically indicate to others that an individual is experiencing pain from a 20-item bank [39–41]. The participant rates their pain behavior in the last seven days on a 6-point scale (no pain, never, rarely, sometimes, often, always).d. **Sleep disturbance** to measure self-reported perceptions of sleep quality, sleep depth, and restoration associated with sleep from a 27-item bank [39–41]. The participant rates sleep disturbance in the last seven days on a 5-point scale (not at all, a little bit, somewhat, quite a bit, very much).e. **Depression** to measure self-reported negative mood (sadness, guilt), views of self (self-criticism, worthlessness), social cognition (loneliness, interpersonal alienation), and decreased positive affect and engagement (loss of interest, meaning, and purpose) [39–41]. The participant rates depressive symptoms in the last seven days on a 5-point scale (never, rarely, sometimes, often, always).f. **Anxiety** to measure self-reported fear (fearfulness, panic), anxious misery (worry, dread), hyperarousal (tension, nervousness, restlessness), and somatic symptoms related to arousal (racing heart, dizziness) from a 29-item bank [42,43]. Participants rate anxiety in the last seven days on a 5-point scale (never, rarely, sometimes, often, always).g. **Neuropathic pain quality scale** is a short (5 items) and practical measure that can be used to identify patients more likely to have neuropathic pain and to distinguish levels of neuropathic pain [44,45].h. **Physical Function** item bank v1.0 includes a total of 124 physical function items across five categories of physical functioning: upper extremity, lower extremity, axial, central, and instrumental activities of daily living [46]. The items can place patients on the continuum of function from extremely low to very high. Using CAT allows for accuracy similar to delivering all the items, but generally only requires delivery of 4–6 items.i. **Emotional Support** item bank v2.0 measures self-reported perceptions of being emotionally supported by others, including feelings of being loved, cared for, and valued, as well as having someone to talk to during times of need. The participant rates their experiences over the past seven days on a 5-point scale (never, rarely, sometimes, often, always).j. **Informational Support** item bank v2.0 measures individuals’ perceptions of having access to useful advice, guidance, or information when needed, especially during times of decision-making or problem-solving. Participants rate their experiences on a 5-point scale (never, rarely, sometimes, often, always).k. **Instrumental Support** item bank v2.0 will be used for self-reported perceptions of receiving practical help from others, such as assistance with chores, errands, or transportation when needed. Participants rate their experiences over the past seven days using a 5-point scale (never, rarely, sometimes, often, always).

#### Data management plan.

Primary data will be collected via paper or electronically through REDCap and stored electronically in REDCap and eventually statistical analysis files on a Department Server. The storage location will be backed up automatically every day. Other data sources include blood tubes that will be stored at -80^o^C. Quality assurance steps will include: 1) built-in range checks and 2) database testing by the study team prior to moving to production mode. The following quality control methods will be used: 1) single entry with random checks of accuracy and 2) extraction and cleaning of data that will be used for analysis every 6 months.

#### Costs and compensation.

All eligible fracture participants will receive up to a total of US $300 in gift cards. Specifically, the participants will be paid US $100 Dollars for each completed visit (visit #2–4). Control participants will receive $50 in gift cards. Participants will receive gift cards at the end of each testing session. In cases where a participant is unable or wishes not to complete all procedures of the study visits, but are willing to complete partial data collection, such as questionnaires, blood draw, and thermography, they will receive a US $25 gift card for each study visit. In addition, participants who attend in-person visits will also receive a parking validation ticket to cover the cost of parking.

### Statistical analysis

#### Data analysis.

Statistical Analyses/Machine Learning will be conducted under the guidance of our biostatistician. Prior to hypothesis testing, descriptive statistics will be computed for each of the outcome measures, e.g., CPM, TS, and immune biomarkers, by time. The spaghetti plot for each measure over time and distributional characteristics (e.g., normality, outliers, and missingness) will be explored. The proper steps (e.g., transformation) will be taken if needed to ensure the assumptions of the procedure for hypothesis testing are met. To address our aims, we will examine differences in pain modulation (TS, CPM) and immune biomarkers among the fracture participants who develop BFNP and those who do not and healthy controls. We expect fracture patients developing BFNP to exhibit (a) enhanced central sensitization and less efficient endogenous inhibition of pain and (b) alterations in immune cell subsets and cell reactivity post-injury and across time when compared to fracture patients who do not develop chronic pain and matched healthy controls. We will use latent growth mixture models (GMM) [45] to classify the patterns of the trajectory for each measurement by evaluating the latent intercept (baseline means) and latent slope (development) into mutually exclusive classes. GMM will then regress those latent variables to the outcome (BFNP, BF no-chronic pain, and Healthy Control) to test the differences of these factors at 2–3-weeks post injury and across time. Trajectories from the GMM (latent intercept and slopes) will be explained by a nominal latent class variable C. The models will include participant characteristics (e.g., age, race, gender, fracture pattern, etc.). When necessary, a quadratic latent growth variable will be tested to fit the GMM model. The models will be evaluated by the model fit indices such as Akaike information criterion (AIC), Bayesian information criterion (BIC), and likelihood ratio test as well as the corresponding profile plots. GMM is a flexible and more accurate method for measuring change than more traditional approaches such as a univariate repeated measures analyses of variance (ANOVA), a multivariate repeated measures ANOVA, or an analysis of covariance.

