### Participants

#### Sample size.

For fracture patients, we will enroll 265 participants who have sustained rotational ankle (specifically AO/OTA 44 types A-C [15]) fractures that are treated operatively. For control patients, we aim to enroll up to 40 healthy adults, who have never sustained a bone fracture. We will attempt to enroll the same percentage of males and females as the fracture patients.

The sample size was calculated based on the limited data from literature and our experiences on prior studies [16–18]. Dietz et al. reported that patients with fracture or trauma that developed complex regional pain syndrome (CRPS) had higher scores for pain, disability and all patient-reported outcomes than fracture controls [18]. Specifically, the effect sizes of the differences between these two groups were calculated as: Cohen’s d = .31 for neuropathic pain symptom inventory (NPSI), d = .34 for current pain, and odds ratio = 7.4 of developing allodynia. Hall et al. reported the percentage of Brief Pain Inventory (BPI – today’s pain) as 55%, 58% and 34% in the 1st, 2nd and 6th months, respectively, among 53 limb fracture patients [19]. In addition, Rbia et al. [7] and Friesgaard et al. [19] reported that about one in four ankle fracture patients would develop persistent neuropathic pain. Data on other outcomes are sparse. Based on the above information and assuming type one error of α = 0.05 and correlation between repeated measures as ρ = 0.6 and ratio for group size as 1:4, we estimated the total sample size needed to achieve sufficient power (β ≥ 0.8) were n = 205 for NPSI, n = 170 for current pain and for allodynia, and n = 213 for BPI. To maximize our ability to detect the differences, we chose the largest sample size n = 213. Our experiences following fracture patients longitudinally revealed 17% attrition rate (internal surveillance data for PREP-IT studies) [17,20]. We conservatively assumed the overall attrition rate to be 20%. Therefore, a total sample of N = 265 (expected to generate 53 BFNP patients) would need to be recruited.

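### The BFNP group hypothesis is tested through a growth mixture model whose latent class adds nothing to a known-group comparison and can cost power if two or more classes are kept

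*Protocol article*

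**What the plan says.** The Data analysis section states the aim as a comparison of known groups: "we will examine differences in pain modulation (TS, CPM) and immune biomarkers among the fracture participants who develop BFNP and those who do not", with healthy controls as a further group. It then names a latent growth mixture model. For each measurement, trajectories are sorted into non-overlapping classes by their latent intercept and slope. BFNP status is not named as an input to that step.

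The next sentence says the model will regress those latent variables to the outcome, listed as the three observed groups, to test differences at 2–3 weeks and over time. It is followed by "Trajectories from the GMM (latent intercept and slopes) will be explained by a nominal latent class variable C". Participant characteristics enter the models.

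The number of classes is not fixed: "The models will be evaluated by the model fit indices such as Akaike information criterion (AIC), Bayesian information criterion (BIC), and likelihood ratio test", together with profile plots. The choice of method is supported by the statement that "GMM is a flexible and more accurate method for measuring change than more traditional approaches", with repeated-measures ANOVA and analysis of covariance as the comparators.

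The Sample size section gives effect sizes "d = .31 for neuropathic pain symptom inventory (NPSI" and "d = .34 for current pain", and bases the calculation on "assuming type one error of α = 0.05 and correlation between repeated measures as ρ = 0.6 and ratio for group size as 1:4". It contains no latent class.

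**The concern.** BFNP status is known for each assessed fracture patient by the 6–9 month visit, from the pain grading scale and the DN4. A comparison of marker level and change between known groups therefore needs no latent class. Placing C between the group and the growth factors leaves three possible tests:

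- **C against group.** A continuous marker is cut into a few categories, which discards information.
- **Growth factors against group.** This is the direct test, and C plays no part in it.
- **Growth factors against group, given C.** C absorbs part of the group difference that the test is meant to detect.

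These are different estimands with different power, and the section does not say which one carries the hypothesis. This is the only hypothesis-testing method described for the two aims; the machine-learning section is predictive. With about 43 BFNP patients analysed there is little power to give away.

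**Working it through.** **1. The plan's own sample sizes.** Inputs from the Sample size section: α = 0.05 (two-sided assumed), ρ = 0.6, ratio 1:4 (shares 0.2 and 0.8), d = 0.31 and 0.34, and power 0.8 (printed as β).

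Total n = (1.960 + 0.842)² × (1 − ρ) / (d² × 0.2 × 0.8)

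- NPSI: 7.849 × 0.4 / (0.0961 × 0.16) = 204.2, so 205. The plan states: "we estimated the total sample size needed to achieve sufficient power (β ≥ 0.8) were n = 205 for NPSI".
- Current pain: 7.849 × 0.4 / (0.1156 × 0.16) = 169.7, so 170, as stated.

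Both match exactly. Other variance factors do not: for d = 0.31, no reduction gives 511–512 and 1 − ρ² gives 327–328. So these two figures reproduce as a direct comparison of two observed groups. The 213 for BPI cannot be derived uniquely, because group-specific rates are not given.

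Direct power at n = 213 by the same formula is Φ(d × √(213 × 0.16 / 0.4) − 1.960):

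- d = 0.31: Φ(2.861 − 1.960) = 0.816
- d = 0.34: Φ(3.138 − 1.960) = 0.881

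At 20% of 213 there are about 43 BFNP patients and 170 others.

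**2. Power when two classes are forced and none exist.** Assumptions not in the protocol: a 0.5 SD shift; intercept, slope and residual variances 0.6, 0.1 and 0.4; class-specific means with a common within-class covariance; modal class assignment. Table 3 schedules sensory testing at three visits and blood at four.

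| Setting | Direct test | Class-by-group | Class-adjusted |
|---|---|---|---|
| 3 visits | 83% | 36% | 66% |
| 4 visits | 89% | 41% | 65% |
| Repeat runs | 85–87% | 34–39% | 61–69% |

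Under the null, the first two settings rejected in 3–7% for all three tests, so the issue is power and not type I error.

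**3. Sensitivity to the assumptions.** A separate simulation used four visits, compound symmetry with ρ = 0.6, 300 runs (error about 3 points) and an effect set for about 80% direct power.

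| Effect on | Within-class variance | Class-by-group | Class-adjusted |
|---|---|---|---|
| Level | allowed | 0.26 | 0.64 |
| Slope | allowed | 0.30 | 0.61 |
| Level | none | 0.57 | 0.43 |
| Slope | none | 0.05 | 0.81 |

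The loss runs from none (0.80 to 0.81) to about 75 points (0.80 to 0.05). Using posterior probabilities in place of modal class raises 0.26–0.30 to 0.35–0.40. With a level shift of only 0.31 SD, direct power is 0.58–0.59, the class test 0.23–0.39 and the adjusted test 0.28–0.50.

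**4. When two classes are real and BFNP concentrates in one.**

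| Separation | Direct | Class-by-group | Class-adjusted |
|---|---|---|---|
| 2 SD | 0.67–0.69 | 0.61–0.64 | 0.17–0.19 |
| 3 SD | 0.72–0.82 | 0.80–0.85 | 0.07–0.08 |
| 4 SD | 0.71–0.73 | 0.75–0.76 | 0.03–0.06 |

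Here the class test loses 5–6 points or nothing. The class-adjusted test fails.

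**5. How often two classes would be kept.** With normal data, no true classes and within-class variance allowed, BIC keeps two in 0–2% of runs and AIC in 24–32%. With no within-class variance, both keep two in every run.

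**The case against.** The strongest reply is that the group test is written down. The sentence before the one on C relates the latent variables to BFNP, no chronic pain and control, and those variables read most naturally as the intercept and slope. On that reading the plan is close to the remedy. This stands, and it rules out a tempting inference: that the analysis only asks whether hidden classes exist. The fit indices and likelihood ratio test are for model evaluation, not for the group hypothesis. What remains is the next sentence, which makes C explain those same growth factors without saying whether the group test is conditional on it.

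A reader might also take a fixed loss, say 17 to 48 points, as a property of this plan. The protocol does not support that. It does not commit to two classes, and BIC would rarely keep two in normal data if within-class variance is allowed. The 0.5 SD shift is an assumption; the protocol's 0.31 and 0.34 belong to other outcomes. The 170 comparators also mix patients without pain and those in the other pain-state group, whereas the main contrast is with no chronic pain. Floor or skew can make BIC choose two classes, but no marker distribution is given, and planned transformation would deal with lognormal skew.

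The rule for choosing the number of classes may sit in an analysis plan that is not shown, so its absence is not the point here. Finally, the accuracy claim for GMM concerns measuring change against ANOVA-type methods. It is background, and it does not compare a mixture with a single-class growth model that uses the known group.

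**Conclusion.** The point holds in a conditional form. The protocol states a known-group hypothesis, the two reproducible sample sizes rest on a direct two-group comparison, and the chosen method inserts a latent class that the comparison does not need and leaves the tested quantity unclear. If two classes are kept without real classes behind them, power falls from about 85% to roughly 35–40% or 60–70%, depending on the test. Those figures assume 43 versus 170 patients and a 0.5 SD shift. Across other assumptions the loss runs from none to about 75 points. There is none if one class is kept and groups are compared on the growth factors. It is small or absent if well-separated classes track BFNP and the class test is used. This is a worthwhile, inexpensive improvement; it does not show that the planned analysis will fail.

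**What to change.** For each marker, make the confirmatory test a single-class latent growth model or linear mixed model with observed group as predictor of intercept and slope:

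Y = β0 + β1·group + β2·time + β3·group×time + covariates + person-level intercept and slope + error

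Test β1 (level) and β3 (change), with the covariates already planned and no C. Healthy controls attend one visit only, so they enter the comparison of level, not the group-by-time term.

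Keep the GMM as a secondary, exploratory description of trajectory types, with the number of classes chosen by BIC plus a bootstrap likelihood ratio test.

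The change is to analysis wording only and needs no new data; the protocol reports that no analysis has been implemented. The downside is that trajectory classes become exploratory findings.
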